#### 3.2 SECONDARY OBJECTIVES

| Objectives                                                                                                                                                                                                                                                      | Outcome measures / Endpoints                                                                                                                                                                                                                        |
|-----------------------------------------------------------------------------------------------------------------------------------------------------------------------------------------------------------------------------------------------------------------|-----------------------------------------------------------------------------------------------------------------------------------------------------------------------------------------------------------------------------------------------------|
| Efficacy                                                                                                                                                                                                                                                 |                                                                                                                                                                                                                                                     |
| To assess the efficacy of the investigational therapy in patients with acute ischaemic stroke on the non-vitamin K antagonist oral anticoagulants with pre-stroke functional status of 0-1 points in mRS compared to placebo using modified Rankin Scale (mRS). | Proportion of patients with excellent functional status assessed with modified Rankin scale (mRS) (mRS 0-1) at 90 days (+/- 3 days) after investigational treatment administration.                                                                 |
| To assess the efficacy of the investigational therapy in patients with acute ischaemic stroke on the non-vitamin K antagonist oral anticoagulants compared to placebo using NIHSS score.                                                                        | Change in NIHSS score from baseline assessed at 7 (+/-1 day), and 90 days (+/- 3 days) after investigational treatment administration.                                                                                                              |
| Safety                                                                                                                                                                                                                                                   |                                                                                                                                                                                                                                                     |
| To assess the incidence of fatal events after the investigational therapy in patients with acute ischaemic stroke on the non-vitamin K antagonist oral anticoagulants compared to placebo.                                                                      | Incidence of deaths:
- Deaths from any cause
- Deaths subdivided by cause
at 7 (+/-1 day), 30 (+/-2 days) and 90 days (+/- 3 days) after investigational treatment administration.                                                         |
| To assess the incidence of non-fatal events after the investigational therapy in patients with acute ischaemic stroke on the non-vitamin K antagonist oral anticoagulants compared to placebo.                                                                  | Incidence of non-fatal events defined as
- Recurrent ischaemic stroke
- Haemorrhagic stroke (ICH or SAH)
- Neurological deterioration (NIHSS)
at 7 (+/-1 day), and 90 days (+/- 3 days) after investigational treatment administration. |

|                                                                                                                                                                                                                                     |                                                                                                                                                                                                                                                                                                                                                                                                                                                                                                                                                                    |
|-------------------------------------------------------------------------------------------------------------------------------------------------------------------------------------------------------------------------------------|--------------------------------------------------------------------------------------------------------------------------------------------------------------------------------------------------------------------------------------------------------------------------------------------------------------------------------------------------------------------------------------------------------------------------------------------------------------------------------------------------------------------------------------------------------------------|
| To evaluate safety of the investigational therapy in patients with acute ischaemic stroke on the non-vitamin K antagonist oral anticoagulants compared to placebo assessed with neuroimaging.                                       | Rate and severity of early (symptomatic and asymptomatic) intracranial haemorrhage detected by neuroimaging:
- CT or MRI at 24hrs (+/- 4hrs) after investigational treatment administration
- CT or MRI at 7 days (+/- 1 day) after investigational treatment infusion and assessed according to European Cooperative Acute Stroke Study (ECASS II) classification.
Note: Symptomatic Intracranial Haemorrhage (sICH) defined as deterioration of stroke severity in NIHSS of $\geq 4$ points with parenchymal haemorrhage type 2 in neuroimaging. |
| To assess characteristics of major clinically significant extracranial bleedings after the investigational therapy in patients with acute ischaemic stroke on the non-vitamin K antagonist oral anticoagulants compared to placebo. | Incidence and severity of major extracranial haemorrhages defined as:
- fatal
- severe enough to require transfusion or surgery
- an absolute decrease in haemoglobin $> 5$ g/dL
- a decrease in haematocrit of $> 15\%$
- bleeding in persistent or temporary serious disability)                                                                                                                                                                                                                                                                  |
| To assess overall safety profile of the investigational therapy in patients with acute ischaemic stroke on the non-vitamin K antagonist oral anticoagulants compared to placebo.                                                    | Incidence and category of AEs reported during the study.                                                                                                                                                                                                                                                                                                                                                                                                                                                                                                           |

### 3.3 EXPLORATORY OBJECTIVES

| Objective                                                                                                                                                                                                                                     | Outcome measure / Endpoint                                                                 |
|-----------------------------------------------------------------------------------------------------------------------------------------------------------------------------------------------------------------------------------------------|--------------------------------------------------------------------------------------------|
| To assess BNP or NT-proBNP plasma levels after the investigational therapy in patients with acute ischaemic stroke on the non-vitamin K antagonist oral anticoagulants after administration of a specific reversal agent compared to placebo. | Change in BNP or NT-proBNP plasma concentration at Day 7 compared to pre-treatment levels. |
| To assess functional independence after the investigational therapy in patients with acute ischemic stroke on the non-vitamin K antagonist oral anticoagulants compared to placebo using Barthel Index scale.                                 | Change in Barthel Index score measured at Day 90 compared to Day 7.                        |
| To assess cognitive function after the investigational therapy in patients with acute ischemic stroke on the non-vitamin K antagonist oral anticoagulants compared to placebo using MoCA scale.                                               | Change on MoCA scale measured at Day 90 compared to Day 7.                                 |
| To assess pre-stroke cognitive function after the investigational therapy in patients with acute ischemic stroke on the non-vitamin K antagonist oral anticoagulant compared to placebo using IQCODE scale.                                   | Assessment of pre-stroke cognitive impairment measured by IQCODE scale at Day 7.           |

|                                                                                                                                                                                                                               |                                                            |
|-------------------------------------------------------------------------------------------------------------------------------------------------------------------------------------------------------------------------------|------------------------------------------------------------|
| To assess “mental” condition (i.e. depression and anxiety) after the investigational therapy in patients with acute ischemic stroke on the non-vitamin K antagonist oral anticoagulants compared to placebo using HADS scale. | Change on HADS scale measured at Day 90 compared to Day 7. |
| To assess duration of the hospitalisation after the investigational therapy in patients with acute ischemic stroke on the non-vitamin K antagonist oral anticoagulants compared to placebo.                                   | Number of days from the hospital admission to discharge.   |

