#### 9.1.4.4 IQCODE SCALE

Informant Questionnaire on Cognitive Decline in the Elderly (IQCODE) is a tool used to assess cognitive impairment in older people. The IQCODE should be used to supplement the other patient administered tools (e.g. Barthel Index); to increase sensitivity and specificity or used in situations where the patient is unable to complete the assessment. IQCODE assessment will be performed at Day 7 +/- 1 day (Visit 3).

IQC Assessment Form (Polish version) is provided in Appendix in [Section 14.1.6](#).

---

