#### 11.5.1.2 BASELINE DESCRIPTIVE STATISTICS

Age, sex, NIHSS, mRS, and Barthel index will be presented for Visit 0 overall and for each treatment arm and treatment group (study treatment and placebo).

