### 11.5.2.3 OTHER EFFICACY ANALYSES

Exploratory endpoints include additional cognitive and functional status assessments:

These endpoints will be analysed using descriptive statistics of the total scores presented by treatment in each study arm and overall, in both tabular and graphical form. In case of the latter, boxplots will be used for analysis of exploratory functional assessments.

- Barthel Index (see [Section 9.1.4.1](#)) - change from baseline Day 7 (Visit 3) and Day 90 (Visit 5) will be assessed using ANCOVA with baseline Barthel Index score and treatment as independent variables. LS mean difference between placebo and active drug with 95% confidence interval will be provided. If either the equal variance or the normality assumption appears to be grossly violated, other methods including an ANCOVA on ranks model or an appropriate transformation of endpoint might be considered.
- MoCA (see [Section 9.1.4.2](#)) - change from baseline (Day 7) to Day 90 will be analysed in the same way as Barthel Index.
- HADS (see [Section 9.1.4.3](#)) assessment of mental condition collected on Day 7 and Day 90 will be analysed in the same way as Barthel Index.
- IQCODE assessment on Day 7 (see [Section 9.1.4.4](#))
- Brain natriuretic peptide (see [Section 9.1.5](#)) change between baseline (Screening visit) and Day 7 will be analysed in the same way as Barthel Index.

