### Ankieta dotycząca sprawności funkcji poznawczych u osób w starszym wieku.

Proszę zastanowić się na tym jaka jest różnica pomiędzy obecnym zachowaniem Pana/i członka rodziny/przyjaciela obecnie w porównaniu do jego/jej zachowania się 10 lat temu. 10 lat temu był rok 20.....

Poniżej opisane są sytuacje, w których osoba której dotyczy ten formularz musi posłużyć się swą pamięcią, inteligencją. Proszę postarać się ocenić, czy przez te 10 lat doszło do pogorszenia lub może poprawy, czy też nie zaszły żadne zmiany w sposobie codziennego zachowania, funkcjonowania badanej osoby w poniżej podanych sytuacjach. Proszę zwrócić uwagę na **porównanie** sposobu zachowania osoby **obecnie i 10 lat temu**.

Jeżeli osoba, której dotyczy ten formularz 10 lat temu zapominała, gdzie odłożyła jakąś rzecz i obecnie także zapomina powinien Pan/i zakreślić odpowiedź:

Brak istotnej zmiany w zachowaniu.

Data : ..... ..

Imię i nazwisko pacjenta: ..... ..

Rodzaj pokrewieństwa / znajomości osoby wypełniającej ankietę

w stosunku do pacjenta: .....

Proszę zaznaczyć zaobserwowane zmiany przez zakreślenie kółkiem właściwej odpowiedzi.

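### The IQCODE objective compares a pre-stroke characteristic between treatment and placebo, and the Day 7 form does not tie the rating to the time before the stroke

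*Protocol*

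**What the plan says.** Sections 1.1.3.3 and 3.3 of the protocol give the exploratory objective as "To assess pre-stroke cognitive function after the investigational therapy" in the trial population, "compared to placebo using IQCODE scale". The endpoint beside it is "Assessment of pre-stroke cognitive impairment measured by IQCODE scale at Day 7".

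Section 9.1.4.4 and the schedule of activities (1.3) place IQCODE at Visit 3 only. Section 9.1.4.4 mentions no pre-stroke reference point. It describes the tool as an addition to patient-administered scales, or as one to be "used in situations where the patient is unable to complete the assessment".

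The form in 14.2.6 instructs the informant: "Proszę zastanowić się na tym jaka jest różnica pomiędzy obecnym zachowaniem Pana/i członka rodziny/przyjaciela obecnie w porównaniu do jego/jej zachowania się 10 lat temu". In English, the informant is to consider how the relative's or friend's behaviour at present differs from ten years ago. The form repeats the present-versus-ten-years instruction with emphasis.

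In the analysis plan, 11.5.2.3 (Other Efficacy Analyses) lists "IQCODE assessment on Day 7" among the exploratory endpoints shown by treatment. The baseline list in 11.5.1.2 does not include it: "Age, sex, NIHSS, mRS, and Barthel index will be presented for Visit 0".

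**The concern.** There are two separate problems.

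1. **The comparison has no possible treatment effect.** Cognition before the stroke existed before randomisation and before any study drug. Comparing it between active treatment and placebo is a check of baseline balance, yet it is written as an objective about therapy and placed under efficacy analyses.

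2. **The rating is not anchored before the stroke.** Inclusion criterion 3 requires a disabling deficit. An informant who follows the form literally about a week later rates the patient with that deficit present. Several items, such as handling money, using household appliances or losing the thread of a conversation, could be affected by it. The score would then carry a pre-stroke label while containing some of the patient's condition after randomisation.

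What is at stake is the meaning of one exploratory score. IQCODE is the only cognitive scale in the schedule aimed at the time before the stroke, since MoCA is first done at Day 7.

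**Working it through.** No sample size, power or error-rate figure is involved. The check sets the relevant sections side by side and adds a scale calculation.

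**What is being measured, and when**

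| Place in the protocol | State being rated | Role given to the score |
|---|---|---|
| 1.1.3.3 and 3.3, objective | before the stroke | treatment versus placebo |
| 1.1.3.3 and 3.3, endpoint | before the stroke, rated at Day 7 | exploratory endpoint |
| 9.1.4.4 | not stated | supplement to or substitute for patient-administered tools |
| 11.5.2.3 | not stated | descriptive display by treatment |
| 14.2.6, instruction | present versus ten years ago | not stated |
| 14.2.6, commentary after the form | present versus ten years ago; later, pre-stroke dementia assessed in the acute phase | informant screening tool |

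The objective, the endpoint and the last part of the commentary point to a pre-stroke rating. The instruction that the informant reads points to the present. Neither the form nor the body of the protocol tells the informant to leave the new stroke out, so nothing joins the two.

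**What a group difference could mean**

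If every informant rated the state before the stroke, a difference between groups would reflect chance imbalance or rating noise. With a planned minimum of 46 patients per treatment group (1.1.9.1 and 11.3), chance imbalance is quite possible. If some informants rated the present state, a difference could also contain the acute deficit and any effect of treatment on it. The score alone cannot separate these.

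**Scale**

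Inputs from the commentary in 14.2.6: 26 items, each scored 1 to 5, with dementia at 104 or more.

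- Range: 26 × 1 = 26 to 26 × 5 = 130, which matches the range stated there.
- No change on every item: 26 × 3 = 78.
- Cut-off as an item mean: 104 / 26 = 4.0, the slight-worsening category.
- Distance from no change to the cut-off: 104 − 78 = 26 points.

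Purely for illustration, with assumed shifts from a starting score of 78:

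- 7 items rated two steps worse: 7 × 2 = 14, giving 78 + 14 = 92, below the cut-off.
- 13 items rated two steps worse: 13 × 2 = 26, giving 78 + 26 = 104, at the cut-off.

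The documents contain nothing to say which shift, if any, is realistic. The second case is simply the one that reaches the threshold.

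**The case against.** The strongest reply comes from the commentary after the form. It presents IQCODE as suited to assessing pre-stroke dementia during the acute phase of stroke, because an informant can complete it without the patient, and reports that fewer than 1% of stroke admissions in the source study lacked a reliable informant. A reader might infer from the form's wording that the tool cannot measure pre-stroke status at Day 7. The documents do not support that. They show that a pre-stroke rating is intended, and some informants may give one unprompted. What remains is that the commentary explains why an informant tool is convenient but contains no instruction about the time point.

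A reader might also infer that any group difference in IQCODE would be a Day 7 treatment effect under the wrong name. That goes too far, since chance imbalance or rating noise could produce one as well.

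A third point is that no formal test is planned. Section 11.5.2.3 gives ANCOVA for Barthel and refers MoCA, HADS and the natriuretic peptide to the same method, but attaches no model to IQCODE. Describing a pre-stroke characteristic by randomised group is what a baseline table does. This stands and lowers the impact. It does not repair the objective, which still asks for a comparison with placebo.

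Finally, documented significant cognitive impairment before the stroke is already an exclusion (criterion 2 in 5.2), and no trial decision depends on the IQCODE cut-off. The protocol does not assign the score to judging balance or interpreting MoCA, so harm through those uses would be conjecture.

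**Conclusion.** The point holds in a limited form. The objective compares between treatment groups something that treatment cannot change, and this follows from the wording alone. The Day 7 form, as worded, does not secure a pre-stroke reference point, so the score may mix in the acute deficit. Whether it does depends on how informants read the instruction, and by how much cannot be derived from the documents.

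The consequence is small. It concerns one exploratory endpoint with a descriptive analysis and does not touch the primary endpoint, the sample size, safety or any planned test. The illustrative shifts should not be read as evidence that cognitively normal patients will be classed as having dementia. This is a worthwhile correction of low priority.

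**What to change.** 1. In 1.1.3.3 and 3.3, remove the reference to investigational therapy and the comparison with placebo from the IQCODE objective, so that it describes pre-stroke cognition in the enrolled patients.
2. Report IQCODE with the baseline characteristics in 11.5.1.2 in place of 11.5.2.3. Label it as collected at Day 7, because that list is otherwise for Visit 0.
3. Add one line to the form in 14.2.6 asking the informant to rate the patient as he or she was just before this stroke, compared with ten years earlier.
4. If current cognition is what is wanted, leave the form as it is and delete the term pre-stroke from the objective and endpoint instead.

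The cost is a few wording changes and one line on the form; the questionnaire, informant and visit stay the same. The small downside is that forms completed before the new line was added answered a different question. This protocol is version 4.0 of December 2022 and enrolment was planned from 4Q2021, so such forms may exist. They should be flagged and shown separately.

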## 4 STUDY DESIGN

### 4.1 OVERALL DESIGN

STROACT is a multicentre, parallel group, randomized, double-blind, placebo-controlled, non-commercial clinical trial to evaluate the efficacy and safety of sequential reperfusion thrombolytic therapy with rtPA (alteplase) in patients with acute ischaemic stroke (AIS) on non-vitamin K antagonist oral anticoagulants (NOAC: dabigatran, apixaban, or rivaroxaban) after administration of a specific antidote (idarucizumab for dabigatran, and andexanet for apixaban or rivaroxaban). Outline of the study design and patient flow in the study is presented in [Section 1.2](#) the graphic form in [Fig 1](#) (Study diagram) and [Fig. 2](#) (Patient screening and enrolment).

The STROACT study comprises 3 study groups with patient allocation based on NOAC taken before the AIS onset. Specific study interventions per study group are then as follows:

**Study group A** (patients receiving dabigatran and with high plasma anticoagulant activity): intravenous administration of idarucizumab followed by an infusion of rtPA (or corresponding placebo for each component of the intervention).

**Study group B** (patients receiving rivaroxaban and with high plasma anti-Xa activity): intravenous administration of andexanet alfa followed by an infusion of rtPA (or corresponding placebo for each component of the intervention).

**Study group C** (patients receiving apixaban and with high plasma anti-Xa activity): intravenous administration of andexanet alfa followed by an infusion of rtPA (or corresponding placebo for each component of the intervention).

Study participants allocated to A, B, or C study group, will be randomized in 1:1 ratio to receive either active treatment or placebo (comparator). All patients who enter the STROACT study, whether allocated to active treatment or control, must be managed according to local acute stroke care protocols, in the same clinical environment. Such protocols are not specified by the clinical trial protocol but will generally include the components of effective stroke unit care.

Patients with symptoms of an acute ischaemic stroke (AIS) admitted to the hospital with no significant disability prior to the current cerebrovascular incident (0-2 points on the modified Rankin Scale [mRS]), and on NOAC treatment as a prevention of thromboembolic events will undergo standard diagnostic procedures and may be considered for inclusion in the STROACT study. Informed consent for participation in the study (signature of the informed consent form [ICF]) must be obtained as soon as possible when the patient is considered a candidate for the study (see [Section 6.3](#)).

After signing ICF and preliminary confirmation of eligibility for the study (see [Section 5 and 6](#)) patients will be allocated to one of the 3 parallel study groups (A, B or C) based on NOAC being taken before the current cerebrovascular event.

All patients MUST have a pre-enrolment brain CT scan (or MRI) to exclude an intracranial haemorrhage. In addition, patients with stroke severity  $\geq 6$  points in NIHHS, or with other clinical indicators suggesting large vessels occlusion (LVO), for example vision, aphasia, and neglect (VAN) assessment, will undergo angio-CT (or angio-MRI) of cerebral arteries to confirm or exclude LVO; patients with LVO may qualify to mechanical thrombectomy (MT) and will not be included in the study.

A blood sample will be obtained to determine anti-IIa/anti-Xa activity (or respective blood concentration of dabigatran in the respective arm of the study), which is assumed to be directly proportional to the plasma concentration of NOAC. Patients with anticoagulant activity  $>50$  ng/ml (or respective blood concentration of dabigatran in the respective arm of the study) qualify to the study treatment i.e., to NOAC-specific antidote administration (followed by intravenous rtPA therapy); patients with anticoagulant activity level  $\leq 50$  ng/mL may qualify to receive thrombolysis

and eventually will not be included in the STROACT study. However, in patients on dabigatran, it is possible to enrol such a subject into the study based solely on a patient's or witness' report on the last intake of the anticoagulant ie, when it was administered within the last 24 hours preceding initiation of the study treatment. In these situations it is obligatory to collect and store blood for post-hoc anti-IIa testing. The procedure is described in the Laboratory Manual.

Eligible patients allocated to each study group will be randomised at 1:1 ratio to receive experimental treatment or corresponding placebo (see section 6.4). Study treatment is composed of sequential intravenous administration of NOAC-specific antidote (or placebo) followed by the infusion of rtPA or corresponding placebo.

Standard diagnostic procedures, allocation to the study group and randomisation should be completed within 3.0 hrs from AIS symptoms onset to minimise the risk of delay to start of the study treatment. Randomisation scheme will include severity of the IS at randomisation (<6 points, and  $\geq 6$  points in NIHSS) as a stratification factor in all 3 study groups (arms).

Administration of rtPA should be initiated within 4.5h time window calculated from the onset of AIS symptoms but no later than 6h in specific circumstances (correctly performed randomisation process and administration of the antidote, unavoidable factors delaying administration of rtPA beyond 4.5 hours).

After receiving study treatment patients will be assessed at 24 (+/-4) hrs (Visit 2), 7 (+/-1) days (Visit 3), 30 (+/-2) days (Visit 4), and 90 (+/-3) days after rtPA bolus treatment administration and collected data will be recorded in the eCRF (please see Schedule of Assessments [SoA] in [Section 1.3](#))

An Independent Data Monitoring Committee (IDMC) will be established before the start patients' enrolment to monitor progress of the clinical study and to ensure participants' safety. This will include reviewing unblinded safety and the efficacy data, estimating the benefit-risk balance during the study and supervising the overall conduct of the study.

The composition and responsibilities of the IDMC will be described in the IDMC charter.

